#### Measures

Table 2 describes the variables, measures and frequency of measurement. A general description of each measure is provided below.

**Table 2 Tab2:** Measures, frequency

	Screening	Pretest	4th session	Posttest	Follow-up
Blood draw	X			X	
Pulmonary function	X			X	
Sleep study	X				
Beliefs about sleep		X	X	X	X
Sleep habits		X	X	X	X
Self-efficacy for sleep		X	X	X	X
Self-efficacy for COPD		X	X	X	X
Mood		X	X	X	X
Insomnia	X	X		X	X
Fatigue		X		X	X
Health information	X				
Clinical assessment		Each session			
Daytime functioning		X		X	X
		X		X	X
Estimated time required	2.5 hrs	2.5 hrs	No additional visit time	3.0 hrs	2.0 hrs

*COPD* chronic obstructive pulmonary disease

#### Moderators

*Inflammation:* we measure C-reactive protein, commonly used as a marker of inflammation. C-reactive protein has been shown to be a valid marker of inflammation in people with COPD [31]. *Functional status:* pulmonary function tests (PFTs) as described in the screening procedures are performed to measure pulmonary functional status at baseline and at posttest.

#### Mediators

*Beliefs about sleep:* the Dysfunctional Beliefs and Attitudes about Sleep Scale (DBAS-30) [29] is used to measure sleep-related beliefs in subjects with insomnia. The scale consists of 30 items in five themes: misattributions or amplification of the consequences of insomnia, diminished perception of control and predictability of sleep, unrealistic sleep expectations, misconceptions about the causes of insomnia, and faulty beliefs about sleep-promoting practices. The modified response scale includes a 10-point Likert scale labeled *strongly disagree* to *strongly agree*. Adequate reliability and validity were demonstrated in older adults with and without sleep problems. The DBAS-30 was sensitive to changes in older adults with insomnia [32, 33]. *Self-efficacy for sleep:* We measure self-efficacy for sleep using the Self-Efficacy Scale for sleep (SES) [34], a nine-item questionnaire including a 5-point Likert scale. Respondents indicate their confidence (*not confident at all* to *very confident*) in falling asleep, staying asleep and obtaining refreshing sleep. Reliability, validity and test-retest reliability of the SES have been demonstrated in older adults [35–38]. *Sleep habits:* the sleep diary and actigraphy are used to measure sleep habits, including the timing of bedtime, naps, time spent in bed and strategies used when awake during the night. *Self-efficacy for COPD:* the COPD Self-efficacy Scale [39] (COPD SES) is used to measure self-efficacy for COPD. The COPD SES is a 34-item questionnaire with five subscales that includes a 5-point Likert scale. Respondents indicate their confidence in managing breathing (dyspnea) during intense emotions, physical exertion, adverse weather or environmental conditions and risk factors. Responses range from *very confident* to *not at all confident,* scoring 5 to 1 with 5 representing higher self-efficacy. Reliability and validity of the COPD SES have been demonstrated in people with COPD [40, 41].

#### Emotional arousal, fatigue and daytime functioning

To minimize response burden while simultaneously achieving high measurement precision, computerized adaptive testing (CAT) versions for fatigue, depression and anxiety (emotional arousal) and physical function from the Patient Reported Outcomes Measurement Information System (PROMIS) is used (www.nihpromis.org). The PROMIS item banks were developed by researchers from the NIH, using item response theory (IRT) for developing subjective measures with a high level of interval measurement precision, approaching the precision of physiological instruments. Participants respond to one item per tablet computer screen and selection of the next item is guided by the participant’s response to a previously administered item.

The PROMIS Fatigue item bank evaluates a range of mild subjective feelings of tiredness to an overwhelming, debilitating, and sustained sense of exhaustion. The depression item bank assesses self-reported negative mood, views of self, and social cognition, as well as decreased positive affect and engagement. Somatic symptoms (changes in appetite, sleeping patterns) are not included, which eliminates consideration of these items’ confounding effects when assessing patients with comorbid physical conditions. The anxiety item bank measures self-reported fear, anxious misery, hyper-arousal, and somatic symptoms related to arousal. The physical function item bank measures self-reported capability rather than actual performance of physical activities. CAT is appropriate for the adult general population and adults with chronic health conditions. CAT is generic rather than disease-specific and assesses the previous 7 days.

### Outcomes (dependent variables)

#### Insomnia

We objectively assess insomnia using the Actiwatch-2® (MiniMitter, Philips Respironics, Carlsbad, CA, USA) actigraph. Scoring of actigraph data with standardized computer algorithms is reliable and valid relative to polysomnography [42, 43]. Editing is done with sleep diary information because actigraphy tends to overestimate sleep during quiet nocturnal wakefulness, but is useful in measuring treatment effects [44]. The accelerometer is worn on the non-dominant wrist for a minimum of 4 days at each data collection. Insomnia variables measured include sleep onset latency (SL, minutes to fall asleep after lights out), wake after sleep onset (WASO, minutes spent wake after sleep onset), number of awakenings after sleep onset (NA), total sleep time (TST) and sleep efficiency (SE, time spent asleep divided by time in bed).

We subjectively measure insomnia severity using the Sleep Impairment Index (SII) [29, 45] and a sleep diary. The SII includes seven items, each rated on a 5-point scale (0 = not at all, 4 = extremely) to evaluate: sleep onset severity, sleep maintenance, early morning awakening problems, satisfaction with current sleep, interference with daily functioning, impairment attributed to the sleep problem, and level of distress caused by the sleep problem. Total scores range from 0 to 28, with high scores indicating greater insomnia severity. Validity and reliability were demonstrated in older people with insomnia [45]. A 6-point reduction is recommended to represent a clinically meaningful improvement in individuals with insomnia [46]. The sleep diary is completed by all CBT-I participants in the morning at breakfast time for a 1-week baseline period. Subjects receiving CBT-I complete sleep diaries daily during the six-session intervention period, for 1 week at the end of the intervention; and for 1 week at the 3-month follow-up. The sleep diary is completed by participants not receiving CBT-I for 1 week at baseline; 1 week at the end of the intervention; and 1 week at the 3-month follow-up. Sleep variables as above including SL, WASO, TST, EMA and SE are derived from the diary. Variables are calculated for each night and a weekly mean is computed. Sleep diaries have demonstrated validity and reliability in measuring insomnia in terms of sleep latency and waking after sleep onset [47, 48].

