### Trial design

We are conducting a 2 × 2 factorial randomized trial where participants are randomized into four groups created by crossing the two factors, CBT-I versus Attention Control (AC)1 and COPD-ED versus AC2 (*N* = 35 each group). Arm 1 is comprised of 6 weekly sessions of CBT-I + AC1; Arm 2 = 6 weekly sessions of COPD-ED + AC2; Arm 3 = 6 weekly sessions of CBT-I + COPD-ED; and Arm 4 = 6 weekly sessions of AC1 + AC2. Each session is approximately 75 min in length. There is follow-up at 3 months post intervention. Dependent variables include objectively and subjectively measured insomnia and fatigue, measured three times: at baseline (pretest, T1), immediately post intervention (posttest, T2), and at 3 months (follow-up, T3) to provide data on the long-term effects of the interventions. In addition to these times, mediator variables are measured after the fourth session to improve our ability to test a causal mediating effect.

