
**Table 3 Tab3:** Study design

Study design	CBT-I	AC1	Main effect COPD-ED
COPD-ED	35	35	70
AC2	35	35	70
Main effect CBT-I	70	70	

*AC1* attention control 1, *AC2* attention control 2, *CBT-I* cognitive behavioral therapy for insomnia, *COPD-ED* COPD education

Aim 2: to define the mechanistic contributors to the outcomes after CBT-I and COPD-ED. We hypothesize that CBT-I and COPD-ED components impact insomnia and fatigue through complementary mechanisms. We have previously shown that CBT-I was related to beliefs about sleep, sleep habits, self-efficacy for sleep, and that COPD-ED was related to management of COPD and emotional arousal, thus making them both appropriate candidates for an insomnia treatment approach for COPD patients. We will employ path analysis to test the conceptual model illustrated in Fig. 1 [70]. The model will test whether each treatment component is related to change in the hypothesized mediator, and whether that change is associated with improvement in the outcome. Direct and indirect treatment effects will be estimated. We will conduct path analyses as follows: (1) specification, (2) identification, (3) estimation, (4) testing of fit, and (5) respecification [71]. Potential moderators suggested by our previous work include gender, initial insomnia and fatigue severity, and inflammation and will be tested as interactions of the effect of each treatment component on the outcomes. Variables found to be a significant moderator of treatment will be tested further to determine if the effect is due to a moderated impact on significant mediator variables. Path models assume that variables used to describe relationships are manifest variables and measured without error. While we recognize that it would be preferable to estimate a measurement model, the feasible sample size for this study precludes more complex modeling. Thus, we acknowledge this limitation and will restrict path analysis to reliably measured variables, that is, with internal consistency of 0.80 or higher. Mplus (version 6) will be used to estimate the path models. The root-mean-square error of approximation (RMSEA) and Bentler’s Comparative Fit Index (CFI) will be reviewed to assess model fit. An adequate fit of the data to the model is indicated by a RMSEA value less than 0.08 and a CFI greater than 0.90.

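### Sleep habits are scheduled at session 4 in every arm, but the arms without CBT-I keep no diary then, so the CBT-I effect on this mediator cannot be estimated from session-4 diary data

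*Protocol article*

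**What the plan says.** All points are in the protocol article.

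- **Timing.** Under Trial design, "mediator variables are measured after the fourth session to improve our ability to test a causal mediating effect". Table 2 (Measures) marks sleep habits at pretest, 4th session, posttest and follow-up, with no exception by arm, and gives the time needed at the 4th session as "No additional visit time".
- **Source.** Under Mediators, "the sleep diary and actigraphy are used to measure sleep habits". The content listed there includes "time spent in bed and strategies used when awake during the night".
- **Diary in the CBT-I arms (1 and 3).** Under Insomnia, "Subjects receiving CBT-I complete sleep diaries daily during the six-session intervention period".
- **Diary in the other arms (2 and 4).** The same section states: "The sleep diary is completed by participants not receiving CBT-I for 1 week at baseline; 1 week at the end of the intervention", followed by one week at the 3-month follow-up. Nothing is scheduled in between.
- **Actigraphy.** The Insomnia section has the device worn for at least 4 days at each data collection and edited with diary information. It does not say whether the fourth session counts as a data collection.
- **Reliability rule.** Under Statistical analysis, Aim 2, the plan "will restrict path analysis to reliably measured variables, that is, with internal consistency of 0.80 or higher". Emotional arousal is measured with adaptive tests: the relevant section specifies "computerized adaptive testing (CAT) versions for fatigue, depression and anxiety (emotional arousal) and physical function".

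**The concern.** The session-4 measurement exists so that the mediator is recorded before the posttest outcome. Changed sleep habits are one of the mechanisms proposed for CBT-I. For the diary part of this mediator, the schedule yields session-4 values only in participants who receive CBT-I, so the path from CBT-I to sleep habits has nothing to be compared with at that time. This is a fault of data collection, and an analysis plan written later cannot restore what was not collected. The Trial status section says that recruitment is ongoing. Every participant in Arms 2 and 4 who passes session 4 without a diary adds to the loss.

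A lesser matter concerns the gate for the path models. The plan defines reliable measurement as internal consistency. In its usual item-level form that index does not fit adaptive tests, in which respondents answer different items, or diary and actigraphy quantities averaged over nights. Read literally, the rule would shut out variables that the plan's own Aim 2 model needs.

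**Working it through.** **1. Number affected.** The plan's own total is 4 × 35 = 140 retained. With 15% attrition, 140 / 0.85 = 164.7, so 165 against the stated 166; the figure is reproduced within rounding, and nothing below depends on the difference. Arms without CBT-I: 2 × 35 = 70 of 140, or 83 of 166 enrolled under equal allocation. That is 50% of the sample and 100% of the non-CBT-I level of the factor.

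**2. Can the path be estimated at session 4?** Regress the session-4 diary value on an intercept, CBT-I (0/1) and COPD-ED (0/1).

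| Arms observed | Rows (intercept, CBT-I, COPD-ED) | Rank | Coefficients |
|---|---|---|---|
| All four | (1,0,0), (1,0,1), (1,1,0), (1,1,1) | 3 | 3 |
| Arms 1 and 3 only | (1,1,0), (1,1,1) | 2 | 3 |

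With Arms 1 and 3 alone, the CBT-I column equals the intercept column, so the CBT-I coefficient is not identified.

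**3. Does the missing-data plan help?** Here missingness is fixed by the assigned arm, which is observed. The plan's classification could thus call it missing at random and pass it to full information maximum likelihood. But no one in Arms 2 and 4 has a session-4 diary value. Any estimate would carry over the relation between visits seen in Arms 1 and 3, an assumption that the session-4 data cannot check.

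**4. Does actigraphy help?** Only in part, and only if it is worn at session 4. It could inform bedtime, time in bed and perhaps naps. It does not record what a person does when awake at night; the Enactment and fidelity section takes that from a diary question. Because the diary is also used in editing, session-4 recordings would be edited differently by arm.

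**5. What remains intact.**

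- Table 2 marks sleep beliefs, both self-efficacy scales and mood at the fourth session, and none of them relies on the diary.
- All arms keep a diary at baseline, posttest and 3 months, so posttest sleep habits have a full comparison.
- Outcomes are measured again at 3 months, after the posttest mediator.

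**6. Reliability rule.** On a literal item-level reading, 3 of 5 mediators qualify for the check (sleep beliefs and the two self-efficacy scales). So do 2 of 13 insomnia and fatigue outcomes (SII and CRQ-F), counting 5 actigraphy + 5 diary + SII + CRQ-F + PROMIS Fatigue = 13. Equivalents of 0.80 exist for the rest:

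- Adaptive test: 1 − SE²/SD² ≥ 0.80 gives SE ≤ √0.20 × SD = 0.447 SD.
- Mean of k nights (Spearman-Brown): the single-night reliability needed is 0.80 / (k − 0.80(k − 1)). For k = 4 this is 0.80/1.6 = 0.50; for k = 7 it is 0.80/2.2 = 0.364.

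**The case against.** The other side has several good points.

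- **Actigraphy is a named second source.** The text allows that it is worn at session 4, so actigraphy-based habits are uncertain at that visit, not shown to be absent. This stands, and it limits the finding to diary-based content.
- **Time order is not lost altogether.** A reader might infer that sleep habits and emotional arousal can no longer be tested with the mediator ahead of the outcome. The document does not support that. Posttest sleep habits precede the 3-month outcome, the Aim 2 text does not fix which visit supplies the change in the mediator, and mood is measured at session 4 in every arm.
- **Most of Aim 2 can proceed.** A reader might also infer that much of Aim 2 cannot be run. Three fixed-scale mediators can be analysed at session 4 with SII or CRQ-F, and sleep habits can be analysed at posttest.
- **The reliability rule has a plain purpose.** It would be too much to say that no coefficient exists for the adaptive, diary and actigraphy measures. The plan averages nightly values, so consistency across nights can be computed, and item-response reliability serves the adaptive tests. Nothing suggests that the authors meant to drop these variables, and a full analysis plan is promised before unmasking. This half is therefore a wording point.

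What these arguments do not remove is the conflict between the diary schedule and Table 2.

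**Conclusion.** The point holds in a limited form. The diary schedule contradicts the session-4 schedule for sleep habits, and the gap coincides exactly with the CBT-I factor: 70 of 140 planned completers, with no comparator left. The CBT-I effect on diary-based sleep habits cannot be estimated from session-4 diary data. One of five mediators is affected, at one of its four measurement times; Aim 1 is not touched and no sample-size figure changes. What is lost is the ordering of this mediator ahead of the posttest outcome, which is the reason the plan gives for measuring at session 4.

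This rests on reading the diary schedule as complete. Whether actigraphs are issued at session 4 is not stated; if they are, the gap narrows but does not close. The reliability wording is secondary and loses no data. Its only added assumption is that SE and SD are on the same score scale.

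**What to change.** Reconcile Trial design, Table 2, Mediators and Insomnia in one of two ways.

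- **(a) Collect the data.** From now on, all four arms keep the diary and wear the actigraph for the week around session 4. The cost is one more week of self-monitoring in Arms 2 and 4, which already do this at three other times, and a minor amendment. Controls enrolled before and after the change will differ in self-monitoring, so record the enrolment period and take account of it in the analysis.
- **(b) Change the analysis time.** Remove the session-4 mark for sleep habits and test this mediator with its posttest value against the 3-month outcome. Label any analysis against the posttest outcome as not temporally ordered. This needs no new data, but gives up the early measurement for this mediator. If enrolment is already complete, it is the only option left.

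Under either option, do not use session-4 diary data from the CBT-I arms alone for the CBT-I path, and state whether the actigraph is worn at session 4.

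In the Aim 2 text, replace internal consistency with reliability of 0.80 or higher. Use alpha for fixed scales, 1 − SE²/SD² for adaptive tests, and multi-night reliability for diary and actigraphy means. This costs one sentence, written before unmasking.

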#### Fatigue

We measure the frequency and intensity of fatigue experienced in the previous 2 weeks using the Chronic Respiratory disease Questionnaire – Fatigue (CRQ-F) [49]. This consists of four items, scored on a 7-point Likert scale. Lower scores indicated more fatigue. The minimal clinically significant change in the CRQ score is associated with a change of 0.5, and a moderate change is associated with a change of 1.0 [50]. In our pilot study, people with COPD reported a mean improvement of 0.75 in mean score of the CRQ-F Scale after CBT-I, suggesting a clinically meaningful improvement in symptoms. Validity and reliability of the CRQ-F was demonstrated in people with COPD [49, 51, 52]. The Cronbach’s alpha for the CRQ-F in our pilot study of people with COPD and insomnia was 0.91. We measure the general feeling of fatigue using the PROMIS Fatigue CAT version described above.

#### Other control variables

We collect demographic information using a questionnaire at the screening visit. We also measure dyspnea using the CRQ Dyspnea Scale (CRQ-D). Participants rate the dyspnea they experience during selected activities that they perform on a regular basis. It is a five-item scale with a potential range from 1 = extremely short of breath to 7 = not at all short of breath. Reliability and validity were reported [53].

### Process measures

#### Health information

A clinical questionnaire is administered at baseline to characterize the sample in terms of demographics and health history. The clinical questionnaire incorporates the ATS-DLD Respiratory Questionnaire that measures dyspnea [54], the Functional Comorbidity Index [55, 56], indicators of socioeconomic status [57], and questions related to smoking status, current medications and treatment. It also includes the modified Insomnia Interview Schedule [29], which is used to explore the nature of each subject’s sleep complaint.

#### Clinical assessment

The Health Report is used to monitor health status during the intervention and the follow-up period. We monitor COPD exacerbations and the use of corticosteroids, using procedures established for a previous study (NR08037). The Health Report Form is a two-page form that is easy to complete in 1 min or less. It includes the Epworth Sleepiness Scale [58] (ESS), which is used to assess daytime sleepiness in the CBT-I group during the intervention period. These data may be tested as covariates in the analyses.

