## Abstract

**Background:**

Difficulty falling asleep, staying asleep or poor-quality sleep (insomnia) is common in people with chronic obstructive pulmonary disease (COPD). Insomnia is related to greater mortality and morbidity, with four times the risk of mortality for sleep times below 300 min. However, insomnia medications are used with caution in COPD due to their potential adverse effects. While cognitive behavioral therapy for insomnia (CBT-I) is effective for people with primary insomnia and people with other chronic illnesses, the efficacy and mechanisms of action of such a therapy are yet unclear in people with both insomnia and COPD. The purpose of this study is to rigorously test the efficacy of two components of insomnia therapy – CBT-I and COPD education (COPD-ED) – in people with coexisting insomnia and COPD, and to identify mechanisms responsible for therapy outcomes. The rationale for the proposed study is that once the efficacy and mechanisms of CBT-I and COPD-ED are known, new and innovative approaches for insomnia coexisting with COPD can be developed to non-pharmacologically minimize insomnia and fatigue, thereby leading to longer, higher-quality and more productive lives for people with COPD, and reduced societal cost due to the effects of insomnia.

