#### CBT-I, COPD-ED and AC interventions

For both groups, sessions consist of six weekly group sessions, 75 min in length, administered in an individual or small-group (two to four persons) setting. The sessions are provided by clinicians trained in CBT-I, COPD-ED and the AC health education. Although the intervention period is relatively brief, we expect that some subjects will miss sessions. Subjects are allowed to make up classes within 2 weeks, for up to two sessions. The CBT-I component is based on Morin [29] and Perlis [30] and includes a program of stimulus control therapy (SCT), sleep-restriction therapy, sleep hygiene, cognitive therapy and relaxation therapy. The COPD education component (COPD-ED) is modeled after the COPD education program used in a previous study. Briefly, topics include how the lungs work; overview of COPD; managing COPD, including techniques for managing dyspnea; discussion of COPD medications; preventing and coping with exacerbations, flu and colds; and preventing complications of COPD. Table 1 summarizes the components of the CBT-I and COPD-ED interventions. These topics are presented using brief PowerPoint presentations, discussion and handouts. The CBT-I + COPD-ED intervention is a combination of CBT-I and COPD education. Each intervention session contains a CBT-I segment and a COPD education segment, for a total of approximately 75 min (Table 1). Topics include managing insomnia and COPD using strategies known to be effective. The AC intervention is comprised of six sessions of social support and general health education. Education excludes sleep and COPD topics and includes information about topics such as cholesterol, blood pressure, color perception, vitamins and memory.

**Table 1 Tab1:** CBT-I and COPD-ED topics

Session	CBT-I	COPD-ED
1	Orientation, “Background on sleep”	Orientation, “How the lungs work”
2	What is insomnia?	What is COPD?
3	Managing insomnia	Managing COPD
4	Managing insomnia, medications	Managing COPD, medications
5	Managing insomnia, techniques	Managing COPD, exacerbations, flu, colds
6	Insomnia relapse prevention	Preventing complications of COPD

*CBT-I* cognitive behavioral therapy for insomnia, *COPD-ED COPD* education, *COPD* chronic obstructive pulmonary disease

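### The Epworth scale is assigned to the CBT-I group only, so sleepiness during sleep restriction has no comparator

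*Protocol article*

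**What the plan says.** **Treatment.** Under CBT-I, COPD-ED and AC interventions, the CBT-I component "includes a program of stimulus control therapy (SCT), sleep-restriction therapy, sleep hygiene, cognitive therapy and relaxation therapy". Enactment and fidelity adds that reported time in bed is compared with a recommended time in bed.

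**Sleepiness.** Under Process measures, Clinical assessment, the Health Report form carries the Epworth scale, "which is used to assess daytime sleepiness in the CBT-I group during the intervention period". The same paragraph says the form takes a minute or less and that its data may be tried as covariates. No other use in analysis is given.

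**Schedule.** The corresponding row of Table 2 reads "Clinical assessment Each session", with no arm restriction. Trial design gives every arm six weekly sessions.

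**Sleep time.** Under Outcomes, Insomnia, the actigraphy variables include "number of awakenings after sleep onset (NA), total sleep time (TST) and sleep efficiency", and for the diary "Sleep variables as above including SL, WASO, TST, EMA and SE are derived from the diary". Trial design sets the outcome times "at baseline (pretest, T1), immediately post intervention (posttest, T2), and at 3 months (follow-up, T3").

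**The concern.** Sleep restriction is a reason to watch sleepiness while treatment is running, and the Epworth is the only sleepiness instrument the article names. The form and the visits exist in every arm, but the stated use of the scale stops at CBT-I.

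The trial could therefore report the efficacy of CBT-I in people with COPD without being able to say whether they became sleepier during treatment than people who did not receive it. This is a matter of data collection, so it cannot be settled in an analysis plan written later.

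**Working it through.** **1. The plan's own sample size, for scale.** Inputs from Power analysis: d = 0.5, two-sided alpha 0.05, power 0.80, 35 retained per cell, 15% attrition. Table 3 gives 70 v 70 for each main effect.
- Needed per factor level: 2 × (1.96 + 0.842)² / 0.5² = 62.8, so 63 (64 by the t test), or 32 per cell. With 70 v 70 the power is 0.84.
- Enrolment: 140 / 0.85 = 164.7, so 165 against the stated 166. The figures reproduce and are not in dispute.

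**2. Who contributes Epworth data.** CBT-I is given in Arms 1 and 3, so the comparison is 35 + 35 = 70 with CBT-I against 0 without. If the singular group in the text means Arm 1 alone, it is 35 against 0. Comparing Arm 1 with Arm 3 would speak to COPD-ED among CBT-I recipients. It would not speak to CBT-I.

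**3. What an uncontrolled course estimates.** Write the mean change over sessions as E + C. E is the effect of CBT-I, and C is everything shared by all arms (time, illness, regression to the mean).
- CBT-I arms alone give E + C, which is one equation in two unknowns.
- With the other arms, (E + C) − C = E.
- Precision is not the difficulty. With 70 participants the uncontrolled mean has a 95% half-width of 1.96 / √70 = 0.23 SD, but for the wrong quantity.

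**4. The covariate use.** In a model of CBT-I v no CBT-I, the Epworth value is missing for everyone without CBT-I. Complete-case fitting leaves only CBT-I recipients, so the treatment indicator is constant and its effect cannot be estimated. Likelihood-based handling would have to extrapolate Epworth values into arms where none were observed. The scale is also measured after randomization and may itself respond to treatment, so adjusting for it could remove part of the effect under study.

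**5. What full collection would give.** The article states no Epworth SD, so 3, 4 and 5 points are assumptions. At 70 v 70:
- half-width = 1.96 × SD × √(2/70) = 0.33 SD, or 0.99, 1.33 and 1.66 points;
- difference detectable at 80% power = 0.4736 × SD, or 1.4, 1.9 and 2.4 points.

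**6. If the change comes during recruitment.** Only participants treated after the change form a like-with-like comparison. The half-width 1.96 × √(2/n) is 0.39 SD at 50 v 50, 0.47 SD at 35 v 35 and 0.62 SD at 20 v 20. These values of n are illustrations, because the article does not say how many had been treated.

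**The case against.** **The wording may describe monitoring, not collection.** The form includes the scale and Table 2 does not limit the form to an arm, so all participants may complete it while staff act on it only for CBT-I recipients. That reading is possible. If it is right, the data exist and a sentence is enough. The text still assigns the scale to one group, so it needs changing either way.

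**Other measures are compared across arms.** CRQ-F, PROMIS Fatigue, the Sleep Impairment Index and daytime functioning are all measured at pretest, posttest and follow-up, and the Health Report tracks exacerbations and corticosteroid use. General daytime worsening would therefore not be invisible at those visits. These instruments do not measure sleepiness, however, and none of the symptom scales is scheduled during the sessions for this purpose.

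**A reader might infer that short sleep also escapes between-arm analysis.** The Abstract describes insomnia as related to mortality, "with four times the risk of mortality for sleep times below 300 min", and sleep efficiency can rise when time in bed falls even if sleep time falls too. The documents do not support the inference. Total sleep time by actigraphy and diary is measured in all arms at T1, T2 and T3. It is an insomnia variable, and insomnia enters the mixed model with treatment × time and two-sided tests (Statistical analysis). At 70 v 70 a difference in mean of about 0.47 SD is detectable at 80% power, so a fall would be estimated and tested. The 300-minute figure is background and is not adopted as a trial threshold. A count below it is a detail the separate analysis plan can settle.

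**Conclusion.** The point holds for the Epworth scale. As written, the trial yields no controlled estimate of sleepiness while sleep restriction is being applied, and the data cannot do the covariate work suggested for them. In numbers it is about 70 against none, where 70 v 70 would give an interval of roughly ±0.33 SD.

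This assumes that the text means what it says about who is assessed, that the CBT-I group covers Arms 1 and 3, and that retention is as planned. The gap does not affect the sample size or the planned efficacy comparisons, and it does not suggest that CBT-I causes harm. It is a modest defect that is cheap to correct and worth correcting while recruitment continues.

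**What to change.** **Change the Clinical assessment paragraph** so that participants in all four arms complete the Epworth items at the same sessions. If they already do, say so and use the data. Remove Epworth from the possible covariates for the CBT-I comparison.

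**Report** CBT-I v no CBT-I over sessions as a descriptive safety comparison, with estimates and 95% CIs and no added significance test. Take session 1 as the reference, completed before that session's content. It falls after randomization but ahead of treatment. If the change is made mid-trial, restrict the comparison to participants treated after it.

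**Cost.** A short scale is added for non-CBT-I participants, on a form the article describes as taking a minute or less, at visits they already attend. Participants already treated contribute no comparator data, so the interval is wider than at full size. No treatment rule changes.

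**Optional.** Beside the sleep-efficiency result, show the number in each arm with weekly mean total sleep time below 300 minutes at T1, T2 and T3. The diary section already provides the summary: "Variables are calculated for each night and a weekly mean is computed".
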